### Eligibility criteria

2.7

The inclusion criteria are as follows:

(1)aged ≥18 years;(2)admitted to hospital within 24 hours after stroke onset;(3)hospitalized with the primary diagnosis of AIS and confirmed by brain CT or MRI and(4)the patient or their close family member sign an informed consent form.

The exclusion criteria are as follows:

(1)the modified Rankin Scale score >1 before the stroke;(2)transient ischaemic attack or subarachnoid hemorrhage;(3)treated with drugs containing NBP before enrollment;(4)history of coagulopathy, systemic bleeding, thrombocytopenia, or neutropenia;(5)history of chronic liver disease, liver and kidney dysfunction, increased alanine aminotransferase (more than 3 times the upper limit of normal value), or increased blood creatinine (more than 2 times the upper limit of normal value);(6)unable to cooperate with 2 MRI examinations;(7)history of severe cardiopulmonary disease, bradycardia (heart rate below 60 beats/min) or sick sinus syndrome;(8)life expectancy is less than 14 days or cannot complete the study due to other reasons;(9)allergic to the drug ingredients in this study; and(10)other unsuitable situations.

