### Ethics

2.2

The study has been approved by the Ethics Committee of Jingjiang People's Hospital (No. 2020-01-006), and it has been registered under the identifier No. ChiCTR2000033486 on the Chinese Clinical Trial Registry on 2020-06-02. Any modifications to the research protocol will be notified to this Human Research Ethics Committee. Informed consent will be obtained from each participant before enrollment. The study bases on the principles of the Declaration of Helsinki and Good Clinical Practice guidelines.

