### Sample size

2.4

We used EpiCalc 2000 for sample size estimation, set significance = 0.05, power = 80%, ratio of cases to controls = 1, risk ratio to detect = 2, proportion (%) controls exposed = 15% (4.4%–24.5%). The sample size was 207 in each of the observation group and the control group.

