### Treatment

3.1

Patients will be grouped immediately after being included in the study. The observation group and the control group will be given NBP injection and NBP injection placebo, respectively, for 14 consecutive days, twice per day. The first injection NBP/NBP placebo should be within 6 hours of stroke onset. In the process of intravenous infusion, a non-PVC infusion set (uniformly equipped by CSPC NBP Pharmaceutical Co., Ltd) must be used. The infusion of NBP time is not less than 50 minutes, and the interval between 2 infusions is not less than 6 hours. If the first infusion start time is after 16:00, then the first day will be given NBP/NBP placebo only once, otherwise 2 times of drugs will be usually given.

We will follow the Chinese guidelines for management of AIS.^[30]^ All patients will receive standards of care, including IVT, endovascular treatment, antiplatelet or anticoagulant therapy based on the patient's condition, nutritional support, and dealing with complications.

Avoid using elixirin, edaravone, or Chinese patent medicine injection containing ginkgo biloba and its extracts during the study. Other medical treatment recommended by the “Chinese Guidelines for the Diagnosis and Treatment of Acute Ischemic Stroke” is permitted.

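### Entry is open to patients admitted up to 24 hours after onset, but the first infusion should be within 6 hours of onset, so patients admitted later can be randomised but not dosed as stated

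*Protocol article*

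**What the plan says.** Inclusion criterion 2 in the protocol article (Eligibility criteria, 2.7) takes in anyone "admitted to hospital within 24 hours after stroke onset". The ten exclusion criteria in the same section do not mention the time at which study drug can be started.

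The Treatment section (3.1) sets the order of events and the dosing time: "Patients will be grouped immediately after being included in the study", and then "The first injection NBP/NBP placebo should be within 6 hours of stroke onset". It makes no exception for patients who arrive later and does not say how they are to be treated.

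Two further steps come before allocation. The Ethics section (2.2) states: "Informed consent will be obtained from each participant before enrollment". Inclusion criterion 3 asks for the diagnosis to be confirmed by CT or MRI.

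**The concern.** Entry and first dose are both timed from stroke onset, but one limit is four times the other, and nothing in the text connects them. The stated criteria therefore let in patients for whom the stated dosing time has already passed.

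Staff faced with such a patient have three options, and the protocol chooses none of them:

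- give the first infusion late, outside the stated limit;
- randomise and then withhold the study drug;
- decline to enrol, using an entry limit that the criteria do not contain.

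Under the first two, treatment differs from what is described. Under the third, the recruited population does. A reader of the results could not tell from the protocol which patients were meant to be studied or how soon after onset they were meant to be treated.

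**Working it through.** The protocol states no derived figure on this point, so there is nothing to reproduce first. The check compares the two limits directly.

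**Inputs**

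- Latest admission: 24 hours after onset (Eligibility criteria, 2.7, criterion 2).
- Latest first infusion: 6 hours after onset (Treatment, 3.1).
- Allocation: immediately after inclusion (Treatment, 3.1).
- Before allocation: consent (Ethics, 2.2) and CT or MRI confirmation (Eligibility criteria, 2.7, criterion 3).

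**Step 1: time left at admission.** For a patient admitted at hour *a*, the time left for imaging, consent, allocation and the start of the infusion is 6 − *a*.

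| Admitted at hour *a* | Meets criterion 2? | Hours left, 6 − *a* |
|---|---|---|
| 3 | yes | 3 |
| 6 | yes | 0 |
| 10 | yes | −4 |
| 24 | yes | −18 |

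Both rules can be followed for patients who arrive early enough. From hour 6 onwards they cannot.

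**Step 2: share of the window.** Hours in conflict: 24 − 6 = 18, and 18/24 = 75%. Hours compatible at most: 6/24 = 25%. Because imaging, consent and allocation must also fit before the infusion, the usable part is below 25%. The documents do not give the duration of these steps, so it cannot be stated more exactly.

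**Step 3: number of patients.** This cannot be computed, because no distribution of arrival times is given. As an assumption only, let *f* be the share of patients meeting the current criteria who can be dosed within 6 hours. The planned total is 2 × 207 = 414 ("The sample size was 207 in each of the observation group and the control group"). The number of eligible patients needed to obtain 414 dosed on time is 414/*f*:

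| Assumed *f* | 414/*f* |
|---|---|
| 100% | 414 |
| 75% | 552 |
| 50% | 828 |
| 25% | 1656 |

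**Step 4: does other timing text resolve it?** No. One rule sets a minimum gap of 6 hours between two infusions, which is a different interval. The other reads "If the first infusion start time is after 16:00, then the first day will be given NBP/NBP placebo only once"; it sets the number of doses on day 1 and does not extend the limit for the first one.

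**The case against.** The strongest reply is that the dosing sentence is advisory. It says should, while the same paragraph uses must for the infusion set. That stands as a point of wording: the 6-hour limit should not be described as absolute. It does not remove the problem, because this is the only time given for the first dose, no exception is stated, and a target that patients admitted after hour 6 cannot meet gives staff no rule for them.

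A second reply is that the last exclusion criterion, a general clause for unsuitable cases, could screen out late arrivals. That would be a discretionary limit at odds with criterion 2. A third is that Figures 1 and 2, which were not available for this check, may show timing. They may clarify the intention, but they cannot make both sentences workable for a patient admitted at hour 10.

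Some stronger readings are tempting but not supported:

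- **Most patients are affected.** The 75% counts hours. Arrivals may be concentrated early.
- **The trial loses its power.** The number affected is unknown, and the result depends on how the effect is read. Suppose, as an assumption, that 30% were removed, leaving 207 × 0.7 ≈ 145 per group. On the stated risk ratio of 2 (15% against 30%), power by the normal approximation is 86.8%, still above the planned 80%. It falls to 64.8% only if the 2 is read as an odds ratio (15% against 26.1%). That reading does come close to the planned 207 (power 79.9%), but it is not what the Sample size section says.
- **The comparison is biased.** No exclusion after randomisation is planned, and Outcome assessment (3.4) collects outcome data from those who complete and those who withdraw. If late patients are dosed late in both groups and kept as randomised, the random comparison is preserved; the likely cost is dilution.
- **The window changes the microbleed rate through reperfusion treatment.** The documents give neither a reperfusion share nor a link to new microbleeds.
- **Sites will differ.** This is a single-centre trial.

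**Conclusion.** The inconsistency is real and stands in the current text. A patient admitted after hour 6 satisfies the listed criteria and is randomised, but cannot receive the first infusion within the stated limit. It covers 18 of the 24 eligible hours, and somewhat more once the steps before allocation are counted. The conclusion rests only on both limits running from stroke onset, which the text states, and on no reconciling text being found in the article.

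The consequence is that the treated population or its treatment timing would depart from the protocol's description, to an extent the documents do not allow one to estimate. No claim about power or bias is needed to support the point.

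**What to change.** Amend the protocol so that Eligibility criteria (2.7) and Treatment (3.1) agree: every patient who meets the entry criteria should be able to receive the first infusion within the stated limit, allowing for imaging, consent and allocation beforehand. Which limit changes, and to what, is a clinical decision for the investigators. Record the time from onset to first infusion for every randomised patient, so that the timing actually achieved can be reported.

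The cost is a short amendment with ethics notification, a registry update and one additional item on the case report form. Depending on the window chosen, the population may be narrower or recruitment slower; the table of assumed shares above shows how widely the recruitment burden could vary, and the centre's own arrival times would settle it.

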### Test drugs

2.8

The observation group and control group will be given NBP injection (NBP and sodium chloride injection 100 mL: NBP 25 mg and sodium chloride 0.9 g; CSPC NBP Pharmaceutical Co., Ltd) and NBP injection placebo (NBP sodium chloride placebo 100 mL, NBP 0 mg, sodium chloride 0.9 g, CSPC NBP Pharmaceutical Co., Ltd), respectively.

## Intervention

3

### Treatment

3.1

Patients will be grouped immediately after being included in the study. The observation group and the control group will be given NBP injection and NBP injection placebo, respectively, for 14 consecutive days, twice per day. The first injection NBP/NBP placebo should be within 6 hours of stroke onset. In the process of intravenous infusion, a non-PVC infusion set (uniformly equipped by CSPC NBP Pharmaceutical Co., Ltd) must be used. The infusion of NBP time is not less than 50 minutes, and the interval between 2 infusions is not less than 6 hours. If the first infusion start time is after 16:00, then the first day will be given NBP/NBP placebo only once, otherwise 2 times of drugs will be usually given.

We will follow the Chinese guidelines for management of AIS.^[30]^ All patients will receive standards of care, including IVT, endovascular treatment, antiplatelet or anticoagulant therapy based on the patient's condition, nutritional support, and dealing with complications.

Avoid using elixirin, edaravone, or Chinese patent medicine injection containing ginkgo biloba and its extracts during the study. Other medical treatment recommended by the “Chinese Guidelines for the Diagnosis and Treatment of Acute Ischemic Stroke” is permitted.

### Brain MRI

3.2

The patients will complete the brain MRI within 48 hours and 14 days after stroke onset. By comparing 2 SWI to evaluate the new CMBs, including whether there are new CMBs, the number of CMBs and the location of CMBs.

The patients will be scanned using a SEIMENS MAGNETOM Avanto 1.5 Tesla scanner. Examinations include SWI, diffusion weighted imaging, T1-weighted imaging, T2-weighted imaging, and fluid attenuation inversion recovery. Diffusion weighted imaging scanning sequence: repetition time = 3400 ms; echo time = 102 ms; flip angle = 90; field of view = 230 × 230 mm; acquisition matrix = 192 × 192 mm; no. of excitations = 1.0; thickness = 6.0 mm; gap = 1.2 mm; scan time = 63 seconds. SWI scanning using a 3 dimension- fast field echo (3D-FFE) sequence as follow: repetition time = 17 ms, echo time = 24 ms, flip angle = 15; field of view = 201 × 230 mm; acquisition matrix = 354 × 512 mm; no. of excitations = 1.0; thickness = 1.0 mm; layer = 100; scan time = 209 seconds.

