### Randomization

2.5

Qualified participants will be randomly assigned to either the NBP group or the control group in a ratio of 1:1. Random numbers will be generated by a random number generator in the SPSS version 20.0 software (SPSS, Chicago, IL), which will be operated by a third party who is uninvolved with the treatment and data collection. The drawn letters (A or B) will be placed into opaque envelopes labeled with sequential numbers. The envelopes will be sealed and remain in numerical order in a safe place till the completion of this study. The same researcher (not involved in the study) will prepare the envelopes.

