### Outcome assessment

3.4

The outcomes will be assessed by independent assessors, who had been trained before participating in this study and blinded to the randomization. All outcome data for participants whether completed or withdrawn during the study will be collected and recorded in the case report form.

Primary outcome: to evaluate the effect of NBP on new CMBs in patients with AIS.

Secondary outcome: to evaluate the effect of NBP on sICH and the National Institute of Health stroke scale score at 14 days of onset.

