### Data analysis

3.7

Statistical analyses will be conducted with SPSS version 20.0 software (SPSS, Chicago, IL). Statistical differences between the 2 groups will be tested using Student *t* test for normally distributed variables or Fisher exact test for dichotomous variables. Two-tailed *P* values < .05 will be considered statistically significant.

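### The primary outcome cannot register a new haemorrhage above the CMB size limit, or a patient lost before the second SWI, yet no effect on new CMBs would be read as safety

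*Protocol article*

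**What the plan says.** All places are in the protocol article.

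- **Brain MRI (3.2):** SWI is done within 48 hours and at 14 days, and the outcome is obtained "By comparing 2 SWI to evaluate the new CMBs".
- **CMBs evaluation (3.3):** the early scan shows old lesions and the day-14 scan shows new ones. The diagnostic criteria require a volume of 2 to 10 mm³. The same section describes the usual diameter as under 5 mm.
- **Outcome assessment (3.4):** new CMBs are the only primary outcome. sICH and the NIHSS score at 14 days are secondary. On withdrawals it states: "All outcome data for participants whether completed or withdrawn during the study will be collected".
- **Adverse events (3.5):** every adverse event from enrolment to last follow-up is recorded, whatever its cause.
- **Introduction (1):** CMBs are chosen because they predict sICH and occur more often. NBP is said to resemble aspirin in its platelet effect, so it might increase new CMBs.
- **Discussion (4):** a finding of no effect on new CMBs is to be taken as establishing that NBP is safe.

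**The concern.** CMBs serve here as a sensitive marker of bleeding risk, but the outcome as defined covers only the mild end of bleeding. It leaves out more serious bleeding in two ways.

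1. **By size.** A patient may have both scans and show a new haemorrhage larger than the limit, with no small lesion beside it. The stated criteria score that patient as having no new CMB. This follows from the definition and is not a missing-data question, so no imputation rule would repair it.
2. **By absence of the second scan.** A patient who dies, or is too ill for MRI because of a bleed, has nothing to compare. Collecting other data on that patient does not supply the scan.

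Under the harm hypothesis in the Introduction, both kinds of event would be more frequent on NBP. The primary comparison could then look reassuring because the worst-affected NBP patients are not events in it, and the Discussion attaches the safety conclusion to that comparison.

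**Working it through.** **Step 1. Where each kind of new bleed is counted**

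| Event by day 14 | Primary (new CMB) | Named secondary outcome |
|---|---|---|
| New lesion of 2–10 mm³, both scans done | Yes | No |
| Larger new haemorrhage, asymptomatic, both scans done | No | None for bleeding |
| Larger new haemorrhage, symptomatic, both scans done | No | sICH |
| Serious bleed that prevents the second SWI | Cannot be scored | sICH, if symptomatic |
| Death before the second SWI, no bleed identified | Cannot be scored | None for bleeding |

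A sphere of 10 mm³ has diameter (6 × 10/π)^(1/3) = 2.7 mm, so the limit is low. If the 5 mm diameter governed instead, the limit would be (π/6) × 5³ = 65 mm³. The gap then starts higher but remains.

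**Step 2. Reproduce the planned size**

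Inputs: "set significance = 0.05, power = 80" percent and control rate 15% (Sample size); two-sided testing, "Two-tailed *P* values < .05 will be considered statistically significant" (Data analysis); 1:1 allocation (Randomization); 207 per arm.

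n = [1.96 √(2p̄(1−p̄)) + 0.84 √(p₁(1−p₁) + p₂(1−p₂))]² / (p₂−p₁)²

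- Effect of 2 read as an odds ratio: p₂ = 2(0.15)/(1 + 0.15) = 0.261. This gives n = 207.3, which matches the stated 207.
- Effect of 2 read as the risk ratio in the text: p₂ = 0.30. This gives n = 121, which does not match.

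The base case below is therefore 26.1% vs 15%, where 207 per arm gives 79.9% power.

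**Step 3. Remove the events that cannot count**

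The document gives no rate for these events, so the rates m are assumptions, apart from 0.9% and 0.4%, which the Introduction quotes for serious bleeding on aspirin plus clopidogrel and on aspirin alone. Every affected patient is taken to be a true bleeding event, which is the worst case. With true rate p:

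- if dropped from the analysis, the observed rate is (p − m)/(1 − m);
- if scored event-free, the observed rate is p − m. This also describes the larger bleed on a completed day-14 scan.

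Worked line for m = 10% (NBP) and 5% (control):

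- Dropped: (0.261 − 0.10)/0.90 = 17.9% and (0.15 − 0.05)/0.95 = 10.5%, a difference of 7.3 points from unrounded rates.
- Event-free: 16.1% and 10.0%, a difference of 6.1 points.

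| m, NBP vs control | Dropped: difference, power | Event-free: difference, power |
|---|---|---|
| none | 11.1 points, 79.9% | 11.1 points, 79.9% |
| 0.9% vs 0.4% | 10.8, 78.0% | 10.6, 77.2% |
| 4% vs 2% | 9.7, 71.9% | 9.1, 68.2% |
| 10% vs 5% | 7.3, 54% | 6.1, 45% |
| 15% vs 5% | 2.5, 11.5% | 1.1, 5.5% |
| 5% vs 5% | 11.7, 88% | 11.1, 88% |

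Two qualifications apply. Equal loss does not mask the effect. At 10% vs 5% the risk ratio hardly moves (1.74 to 1.70 or 1.61); the loss is in the difference and the power. If the true rates were 30% vs 15%, power at 10% vs 5% would fall from 96% to 87% (dropped) or 82% (event-free).

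**Step 4. The same in patients, at the Introduction's rates**

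0.009 × 207 = 1.9 and 0.004 × 207 = 0.8, so about 2 and 1 serious bleeds. Take 31 patients with new CMBs per arm (0.15 × 207 = 31).

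- Complete cases: 31/205 vs 31/206, ratio 1.00.
- Counting the bleeds: 33/207 vs 32/207, ratio 1.03.

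**The case against.** **The harm is not lost to the trial.** A reader might infer that serious bleeding is hidden altogether. The document does not support that: sICH is a named secondary outcome that needs no paired SWI, outcome data are collected on patients who withdraw, and all adverse events are recorded. What stands is narrower. The harm is outside the primary comparison, the Introduction itself calls sICH too infrequent to be sensitive, and the Discussion rests the safety conclusion on CMBs.

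**No rule for unscanned patients is stated.** A reader might infer that they will be dropped or counted event-free. The article says neither. Analysis sets and imputation are ordinary content of an analysis plan, so their absence here is no finding. The size limit is different, because the protocol itself fixes it.

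**Exclusions 6 and 8.** The wording "unable to cooperate with 2 MRI examinations" and "life expectancy is less than 14 days or cannot complete the study due to other reasons" might be read as removing randomised patients later. Both stand in the eligibility list and Treatment groups patients after inclusion, so they read as screening judgements. They should, if anything, reduce missing second scans.

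**The effect may be small.** At the Introduction's rates it is. Some patients with sICH will also reach the day-14 scan, and small lesions beside a large bleed still count. One could assume 10 major bleeds on NBP and none on control, which moves the ratio from 1.05 (31/197 vs 31/207) to 1.32 (41/207 vs 31/207), but that is an extreme case. On the other side, the quoted rates come from antiplatelet treatment, while this trial also permits thrombolysis, endovascular treatment and anticoagulation, so they need not be an upper bound.

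**A composite primary outcome would be worse.** In that extreme case, Fisher's exact test gives p = 0.002 for major bleeds alone (10 vs 0) and p = 0.24 for the composite (41 vs 31). Merging can dilute the signal, and it changes the trial's question. This objection stands, and the fix respects it.

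**Conclusion.** The point holds in limited form. As defined, the primary outcome scores a patient whose only new lesion is above the size limit as event-free, leaves an asymptomatic one outside every named outcome, and cannot score a patient lost before the second SWI. A null result on new CMBs therefore cannot establish safety by itself.

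The bias runs towards no difference only if these events are sufficiently more frequent on NBP. Its size is an assumption: about 2 to 3 points of power at the Introduction's rates, and power of about 45–54% at 10% vs 5%. These figures rest on true rates of 26.1% vs 15% and on every affected patient being a true event. The document supports neither concealment of harm from the trial nor removal of randomised patients through the exclusions.

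**What to change.** 1. Keep new CMBs as the primary outcome, and sICH as a separate secondary outcome.
2. Prespecify one key supportive analysis in all randomised patients. An event is any new CMB, any new intracranial haemorrhage of any size on a scan up to day 14, or death before the second SWI. How to handle surviving patients with no second SWI and no known bleed can be left to the analysis plan.
3. Reword the Discussion so that no effect on new CMBs supports safety only if this analysis and sICH agree with it.

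The cost is some wording and one more analysis, using scans already made. The drawback is that bleeds found on unscheduled scans depend on clinical indication, so ascertainment is less uniform than for the two planned SWIs. This is one reason to keep the analysis supportive.
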